## Methods/Design

### Study design

A multi-centre, single-blinded randomized controlled trial (RCT) with 6 months follow-up will be conducted to evaluate the efficacy of exercise therapy and CBT compared to usual care in patients with PPS (Figure 1). To gain insight into patients' expectations and experiences, a responsive evaluation will be conducted. To determine the cost-effectiveness, an economic evaluation will be conducted alongside this RCT. The study protocol was approved by the Medical Ethics Committee of the Academic Medical Centre (AMC) and all participating centres granted approval to participate.

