### Study population

All patients will be recruited from outpatient clinics of the AMC Amsterdam; the University Medical Centre Utrecht (UMCU); the University Medical Centre Nijmegen (UMCN) or the affiliate rehabilitation centres. Case histories are checked to screen for potentially eligible patients. Patients willing to give signed consent are evaluated by a physician to check in and exclusion criteria (Table 1). The sample size was calculated for this three-arm trial based on the comparison treatment (exercise therapy or CBT) versus usual care, with equal allocation across treatment arms and 4 repeated measurements (at entry (pre-treatment), at 4 months (post-treatment), at 3 months follow-up (short-term follow-up) and at 6 months follow-up (long-term follow-up), respectively), with an estimated correlation coefficient of the repeated measurements of rho = 0.79 (based on unpublished data from a reproducibility study in 37 PPS patients), a clinical relevant improvement of 8 points on the CIS-fatigue scale (for both treatments) [17] and an estimated standard deviation in each treatment group of 9.3. The total sample size needed to detect this difference on a 5% level of significance (two tailed) with a power of 90% was 24 subjects in each group [21]. We expect a drop-out rate of maximal 10%, based on a previous trial in this patient group [22]. Therefore 81 patients will be recruited.

**Table 1 T1:** In- and exclusion criteria

Inclusion criteria
(1) diagnosis of PPS according to the criteria of March of Dimes [1]

(2) severe perceived fatigue (CIS-fatigue > = 35) [47]

(3) age between 18 and 75 years

(4) life-expectancy longer than one year

(5) walking-ability at least indoors with or without a walking aid

(6) ability to cycle on a cycle ergometer against a load of at least 25 Watt

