### Statistical Analyses

GEE (generalized estimated equations) analyses will be used to investigate differences in the effects (primary and secondary outcomes) between both intervention groups and the usual care group and to investigate associations between potential effect modifiers and effect of interventions. Data will be analyzed according to the intention-to-treat principle. Missing data will be imputed by carrying the last observation forward.

The economic evaluation will also be performed according to the intention-to-treat principle. First, mean differences in QALYs will be tested using parametric tests, and uncertainty expressed by 95% confidence intervals. Second, we will conduct between-group comparisons of the mean costs for each of the resource use categories and total costs. Confidence intervals around the mean cost differences will be obtained by a bias-corrected and accelerated (Bca) bootstrapping based on 5000 replications [44]. Third, the incremental cost-effectiveness ratio (ICER) will be determined by dividing the mean difference in total costs by the mean difference in effects. Insight into the uncertainty around the mean ICER will be obtained by bootstrapping based on 5000 replications, the generation of cost-effectiveness planes [45] and cost-effectiveness acceptability curves [46]. Sensitivity analyses involving the most important cost drivers will be performed in order to assess the robustness of the results.

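### Last observation carried forward is the only rule for missing outcomes; it can bias the follow-up contrasts in either direction, modestly at the planned dropout, and no sensitivity analysis tests it

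*Protocol article*

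**What the plan says.** The Statistical Analyses section of the protocol article states the model, "GEE (generalized estimated equations) analyses will be used to investigate differences in the effects (primary and secondary outcomes"), then the analysis set, "Data will be analyzed according to the intention-to-treat principle", and then the missing-data rule, "Missing data will be imputed by carrying the last observation forward". No reason is given for the rule. The only sensitivity analyses named belong to the economic evaluation: "Sensitivity analyses involving the most important cost drivers will be performed in order to assess the robustness of the results".

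Study population and Table 3 set four measurements: T1 before treatment, T2 after treatment at 4 months, and T3 and T4 at 3 and 6 months of follow-up. Study design describes the trial in the same way: "A multi-centre, single-blinded randomized controlled trial (RCT) with 6 months follow-up will be conducted". On dropout, Study population says "We expect a drop-out rate of maximal 10%, based on a previous trial in this patient group". It does not say when patients are expected to leave, or from which arm.

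**The concern.** Carrying the last value forward assumes that a patient stays at exactly the last recorded score. Two departures from that assumption matter here, and they pull in opposite directions.

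- A patient who leaves after T2 keeps the end-of-treatment score at T3 and T4. If benefit fades once treatment stops, the fading goes unrecorded and the effect looks more durable than it is.
- A patient who leaves before T2 keeps the entry score at all later visits. If the treatment works, that patient is counted as unchanged and the effect is diluted.

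The direction of the error therefore depends on dropout timing and on the course of the effect, and neither is known in advance. The Discussion counts the long-term follow-up among the study's strengths, and those are the visits at which the rule supplies an assumed answer. Because this is a stated rule and not a gap, a separate analysis plan could not simply fill it in; the sentence has to change.

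**Working it through.** **Inputs.** All are from Study population: target difference 8 points on CIS-fatigue, SD 9.3, correlation 0.79, four measurements, "5% level of significance (two tailed"), 90% power, dropout at most 10%.

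**The plan's own figure.** For a group difference averaged over T measurements, n per group = 2 × [SD × (z₀.₉₇₅ + z₀.₉₀) / δ]² × [1 + (T − 1)ρ] / T.

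- First factor: 2 × [9.3 × (1.960 + 1.282) / 8]² = 28.40.
- Second factor: (1 + 3 × 0.79) / 4 = 0.8425.
- Product: 23.93, so 24. This agrees with "with a power of 90% was 24 subjects in each group".
- With dropout: 24 / 0.90 = 26.7, so 27 per arm and 3 × 27 = 81.

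**Bias from carrying forward.** In each arm, the bias at a visit is the sum over dropout times of (share leaving) × (mean change at last visit seen − mean change at this visit). The contrast takes the difference between arms. Assumptions: usual care is flat, 10% drop out in each arm, dropout is unrelated to outcome, and leavers would have followed the same mean course as those who stay. Effects are points of benefit over usual care.

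| Dropout timing | True effect at T2, T3, T4 | T4 estimate | T4 error |
|---|---|---|---|
| All after T2 | 8, 4, 0 | 0.10 × 8 + 0.90 × 0 = 0.8 | 0.8 too high |
| All after T2 | 8, 6, 4 | 0.10 × 8 + 0.90 × 4 = 4.4 | 0.4 too high |
| All after T2 | 8, 8, 8 | 0.10 × 8 + 0.90 × 8 = 8.0 | none |
| All before T2 | 8, 8, 8 | 0.10 × 0 + 0.90 × 8 = 7.2 | 0.8 too low |
| All before T2 | 8, 6, 4 | 0.10 × 0 + 0.90 × 4 = 3.6 | 0.4 too low |
| One third in each interval | 8, 4, 0 | (0.10 / 3) × (0 + 8 + 4) + 0.90 × 0 = 0.4 | 0.4 too high |

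In the last row the estimates at T2 and T3 are (1 − 0.10/3) × 8 = 7.73 and (0.10/3) × (0 + 8) + (1 − 0.20/3) × 4 = 4.0. The average over T2 to T4 is (7.73 + 4.0 + 0.4) / 3 = 4.04 against a true 4.0, so nearly all of the error sits at T4.

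**Effect on the T4 test.** Simulation used 27 per arm, SD 9.3, exchangeable correlation 0.79 and adjustment for baseline.

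- Full fade, all dropout after T2: the 5% test rejects in about 8% of trials (8.1% to 8.3% across runs with model-based standard errors), against 5.2% with complete data. As a rough check, the standard error is about 1.7, so the shift is 0.8 / 1.7 = 0.47 standard errors, and Φ(−1.49) + Φ(−2.43) = 0.068 + 0.008, or about 7.6%.
- Full fade, dropout spread over the intervals: 5.9%.
- No effect at any visit: 4.4% to 5.5% across runs, that is, about nominal.

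If dropout were 20%, twice the protocol's maximum, the biases double (0.20 × 8 = 1.6 points) and the first rejection rate rises to about 15%.

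**The case against.** The strongest reply is that the damage is small. The 0.8-point figure needs every dropout to fall in one interval, together with either complete fading or a fully sustained effect. The protocol supports none of these specifically. With dropout spread out, the error is about 0.4 points at T4 and hardly visible in the average over visits. A treatment that does nothing at any visit does not gain false positives when dropout is balanced and unrelated to outcome. The inflated T4 rejection arises only for a treatment that did work at T2. A patient who leaves early may also gain nothing, and then the entry score is not far wrong. All of this stands, and it limits the severity. It does not supply a reason for making carry-forward the sole, untested rule.

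A reader might infer more than the document supports:

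- *That the rule contradicts the sample size.* It does not. Carried-forward values add no new information, so recruiting 27 to offset losses is compatible with keeping everyone in the analysis.
- *That a progressive disease makes a frozen score implausible.* The Background describes complaints arising decades after the epidemics, the CBT section speaks of slow progression, and T2 to T4 is six months. Progression common to all arms cancels when dropout is balanced, and none of the figures above rests on it.
- *That carry-forward corrupts the cost data.* The rule closes the paragraph on GEE, and the economic evaluation starts a new one. The article does not say that the rule reaches the cost diaries, and a missing-cost rule may be left to the full plan.
- *That false positives approach 10%.* Robust standard errors can give 9.8% in the worst case, but they already give 6.1% with complete data at this sample size, so part of that excess is not due to carry-forward.
- *That dropout will differ between arms.* The active arms ask more of patients, so this is possible, but the protocol gives no rates by arm.

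**Conclusion.** The point holds as a modest defect that should be fixed. Carry-forward is the only stated rule for missing outcomes, it is untested, and it can err in either direction at the visits meant to show whether benefit lasts. At the protocol's maximum dropout of 10%, the error in the scenarios examined is at most about 0.8 points, or 0.8 / 8 = 10% of the target difference, with T4 rejection of about 8% instead of about 5% in the worst fading case. In milder scenarios it is 0.4 points or nothing. The sizes rest on assumed dropout timing and fade, a flat usual-care arm, and dropout that is balanced and unrelated to outcome. Unequal or outcome-related dropout could give different figures. The sample size itself reproduces and need not change.

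**What to change.** Replace the carry-forward sentence. The primary analysis should use all observed T2 to T4 values with baseline in the model, by one of two routes: a likelihood-based linear mixed model without imputation, or multiple imputation followed by the planned GEE. Both are valid when data are missing at random. Ordinary unweighted GEE on the observed values alone generally needs the stronger condition that data are missing completely at random, so simply deleting the sentence is not enough.

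Add one delta-adjusted sensitivity analysis for data missing not at random. Keep carry-forward at most as a further sensitivity analysis. Fix the choice before unblinding.

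The cost is a few lines of text, routine programming and possibly slightly wider intervals. No extra patients or measurements are needed.

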#### Economic evaluation

Cost-effectiveness and cost-utility will be evaluated from a societal perspective. The costs will include direct health care costs of visits to general practitioners, medical specialists, therapists, medications and assistive devices, direct non-health care costs i.e. non-reimbursable costs for complementary medicine and over-the-counter medication, and indirect, non-health care costs of changes in paid and unpaid work. All these data will be collected via cost diaries.

Resource use will be valued following the procedures outlined by the Dutch Manual of Costing [40]. Where standard cost prices are not available, tariffs or professional fees will be used to estimate costs. The costs of medications will be estimated using the prices reported by the Royal Dutch Society for Pharmacy. Productivity loss costs from paid work will be estimated using both the human capital approach and friction cost method. The productivity loss costs from unpaid work will be determined using a shadow price. Cost prices of the interventions will be determined by a bottom-up calculation.

The effect measures used in the economic evaluation will be our primary outcome measure fatigue and HRQoL measured with the EuroQol-5D [41] at the four different time measurements. Utilities will be derived using the Dutch tariffs and used to determine quality-adjusted life years (QALYs) [42,43].

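### The QALY difference and the cost-utility ICER are specified without adjustment for baseline EuroQol-5D, which gives up precision that is free to recover

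*Protocol article*

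**What the plan says.** The Statistical Analyses section of the protocol article sets out the economic evaluation in ordered steps. The first is: "First, mean differences in QALYs will be tested using parametric tests, and uncertainty expressed by 95% confidence intervals". Costs are compared next, with bootstrapped intervals. Then "the incremental cost-effectiveness ratio (ICER) will be determined by dividing the mean difference in total costs by the mean difference in effects", with 5000 bootstrap replications, cost-effectiveness planes and acceptability curves to show uncertainty. The robustness checks are limited to costs: "Sensitivity analyses involving the most important cost drivers will be performed in order to assess the robustness of the results".

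The Economic evaluation section says that the effect measures "will be our primary outcome measure fatigue and HRQoL measured with the EuroQol-5D [41] at the four different time measurements". The utilities are converted to QALYs with the Dutch tariffs. Table 3 lists the EuroQol-5D at T1 (pre-treatment), T2, T3 and T4, so the baseline utility is available and enters the QALY.

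GEE appears in a separate paragraph, for "differences in the effects (primary and secondary outcomes) between both intervention groups and the usual care group". The Randomization and blinding section names centre as the only stratification factor.

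**The concern.** A QALY accumulated from entry includes the pre-treatment utility, which treatment cannot have affected. That utility also predicts the later ones. If the arms differ at T1 by chance, a plain difference in mean QALYs carries the imbalance twice: directly, through the weight of T1, and indirectly, through correlation with T2 to T4. Nothing in the design balances utility, and the arms are small.

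The stated method therefore accepts variation that one already collected covariate would largely remove. Cost-effectiveness is one of the five research questions and will be answered from one realised sample. If no rule is set beforehand and an imbalance appears, the choice between a raw and an adjusted ICER would be made after the data are seen.

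**Working it through.** **1. The plan's own figure.** The inputs in Study population are SD 9.3, difference 8 CIS points, rho 0.79, 4 measurements, two-sided 5% and power 90%.

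n = 2(1.960 + 1.282)² × 9.3²/8² × (1 + 3 × 0.79)/4 = 28.40 × 0.8425 = 23.93, so 24 per group. Dropout of 10% gives 24/0.9 = 26.7, so 27 per arm and 3 × 27 = 81. Both stated figures reproduce. The article states no figure for the QALY analysis.

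**2. Inputs for the check.**
- From the article: 27 per arm; visits at entry and 4 months, then 3 and 6 months of follow-up. Read as counted from the end of treatment, these are months 0, 4, 7 and 10.
- Assumed, because the article does not give them: trapezoidal interpolation, utility SD 0.15 to 0.25, and one common correlation r of 0.4 to 0.79 between visits. The upper end borrows the article's value for CIS-fatigue, which is a different scale.

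**3. Weights.** The trapezoidal rule gives the four visits 2, 3.5, 3 and 1.5 months, 10 in total. Baseline utility carries 2/10 = 20% of the weight.

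**4. Carry-over of a baseline imbalance.** The expected shift in the QALY difference per unit of T1 imbalance is b = (2 + 8r)/12. The SE of the imbalance is SD × √(2/27) = 0.272 × SD, that is 0.041, 0.054 and 0.068 for SD 0.15, 0.20 and 0.25. The shift for a one-SE imbalance is:

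| r | b | SD 0.15 | SD 0.20 | SD 0.25 |
|---|---|---|---|---|
| 0.4 | 0.433 | 0.018 | 0.024 | 0.029 |
| 0.6 | 0.567 | 0.023 | 0.031 | 0.039 |
| 0.79 | 0.693 | 0.028 | 0.038 | 0.047 |

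**5. Gain from adjustment.** In units of SD², the variance of one patient's QALY is v = r(10/12)² + (1 − r)(2² + 3.5² + 3² + 1.5²)/144 = 0.694r + 0.191(1 − r). Baseline utility explains R² = b²/v of it, and the ratio of adjusted to raw SE is √(1 − R²).

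| r | v | R² | SE ratio | SE reduction |
|---|---|---|---|---|
| 0.4 | 0.392 | 0.479 | 0.72 | 28% |
| 0.6 | 0.493 | 0.651 | 0.59 | 41% |
| 0.79 | 0.589 | 0.817 | 0.43 | 57% |

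At SD 0.20 and r = 0.6, the raw SE is 0.20 × √0.493 × 0.272 = 0.038 and the adjusted SE is 0.023. These are large-sample values; they ignore the small cost of estimating the slope.

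**6. Fatigue ICER (secondary).** Taking the article's SD of 9.3 as the baseline SD, a one-SE imbalance in CIS-fatigue is 9.3 × 0.272 = 2.5 points. If follow-up scores are compared, 0.79 × 2.5 = 2.0 points carry over. If change scores are compared, about 0.21 × 2.5 = 0.5 points carry over in the opposite direction. The article does not say which is meant, or whether the GEE estimate supplies the denominator.

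**The case against.** The strongest reply is that nothing here is invalid. Allocation is randomised, so the raw QALY difference is unbiased over repeated randomisations. Chance imbalance is ordinary sampling variation, already inside the 95% interval and inside a bootstrap that resamples patients with their baseline values. The middle case shows it: 0.031² + 0.023² is approximately 0.038², so the shift is a component of the raw SE and not an extra error. This stands. A reader might infer that the planned ICER is biased, or that bootstrapping conceals the problem; the documents support neither. What remains is that the bootstrap is centred on the realised difference: it displays the uncertainty but does not reduce it.

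A second reply is that a parametric test of a mean difference does not exclude a regression contrast, and that a condensed article may leave covariates to a full protocol or SAP. This limits how firmly the method can be called unadjusted. Even so, the article names the estimator and the form of the ICER, and the natural reading has no baseline term.

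Two further inferences fail. One is that the imbalance rivals the QALY gain to be expected: the documents state no expected gain. The other is that both ICERs lack the same covariate, or that the fatigue denominator conflicts with the GEE result. For fatigue the relevant covariate is T1 CIS-fatigue, and the article speaks of effects both for the GEE contrasts and for the ICER, so the GEE estimate may be what is divided.

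**Conclusion.** The point holds as a free improvement in precision, not as an error that invalidates the economic evaluation. The stated QALY comparison and cost-utility ICER name no adjustment for T1 utility. Adjustment would lower the SE of the QALY difference by about 28% to 57% and remove an expected shift of about 0.018 to 0.047 QALY per one-SE imbalance. These sizes rest on the assumed SD, correlation and trapezoidal rule. That adjustment helps does not depend on the exact values, provided baseline and later utilities are positively correlated. The sample size and the efficacy analysis are unaffected. The fatigue ICER is a matter of clarification only.

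**What to change.** State before analysis that:

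- incremental QALYs are estimated by regression on arm, with T1 EuroQol-5D utility and centre (the stratification factor) as covariates;
- this adjusted difference is the denominator of the cost-utility ICER;
- the regression is refitted in each of the 5000 bootstrap samples, resampling cost-effect pairs within arm, and the plane and acceptability curve are built from those replicates;
- the fatigue effect in the cost-effectiveness ICER is adjusted for T1 CIS-fatigue, so that it agrees with the trial's efficacy estimate.

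The unadjusted QALY difference can be kept as a sensitivity analysis. The cost is a few lines of analysis code. Both baseline measures are already collected at T1, so no new data, visits or patients are needed.

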## Discussion

In the FACTS-2-PPS study, the efficacy of exercise therapy and CBT in reducing fatigue and improving activities and HRQoL in patients with PPS will be evaluated in comparison with usual care. This study captures some important strengths.

Firstly, the majority of studies on exercise in PPS evaluated the effects of strength or aerobic training in PPS separately. However, to execute normal every day activities, more integrated functional tasks are necessary requiring a combination of strength, endurance, flexibility, balance and coordination. This study evaluates a multi-component exercise training in which aerobic, strength and functional exercises are combined.

Secondly, although it is widely recommended that behavioural adaptation is an important component in the management of fatigue in PPS, there are no studies confirming the effectiveness of this approach. This is the first study that will evaluate the efficacy of CBT in reducing fatigue in PPS. The treatment protocol was developed by investigators with broad experience with CBT for chronic fatigue syndrome and fatigued cancer survivors, and customized to the specific aspects of fatigue in PPS.

Thirdly, the long-term follow-up, the broad arsenal of outcome measures on different domains of the ICF and the inclusion of a responsive evaluation and an economic evaluation gives this study a unique mixed methods design. Investigating patient perspectives and possible discrepancies between perspectives of patients and professionals will help to elaborate strong and weak points of both interventions, which in turn might explain specific results obtained in the study. Additionally, this mixed methods design will facilitate the decision making with respect to implementation of the results when the interventions turn out to be effective.

However, the study has also some limitations. The sample size was based on the detection of an approximately equal effect size of exercise training and CBT in comparison to usual care. Detecting differences in effectiveness between both interventions would require much larger sample sizes. Furthermore, the design of this study, will not give insight into the indicators that are helpful in decision making about tailoring interventions.

In conclusion, the results of this study will provide greater insight on evidence-based treatment options for PPS. Successful outcome from the study has the potential to result in reduced fatigue and improved activities and quality of life for patients with PPS. Results might lead to alterations of existing international guidelines.

